### 8.3.3. Model priors

The prior distribution of  $\alpha_j$  is specified on the probability scale:

$$\alpha_j = \text{logit} \left( \sum_{k=-1}^j \pi_k \right), j = -1, \dots, 89$$

where

$$\pi_{-1}, \dots, \pi_{90} \sim \text{Dirichlet}(\phi_{-1}, \dots, \phi_{90});$$

with hyperparameters,  $\phi_j$ , specified based on the observed rates of home days across all states in pre-trial data (see Appendix) and providing 1 patient's worth of information so that  $\sum_{h=-1}^{90} \phi_h = 1$ . The vector  $\boldsymbol{\phi}$  consists of concentration parameters with a weight of 0.133 on -1 (death), 0.005 on 0-19 (split evenly), 0.017 on 20-39 (split evenly), 0.017 on 40-49 (split evenly), 0.026 on 50-59 (split evenly), 0.042 on 60-69 (split evenly), 0.077 on 70-79 (split evenly), 0.228 on 80-89 (split evenly), and 0.454 on 90.

Because of the large ordinal scale, it is likely that some levels of the ordinal endpoint will be quite sparse. By using a prior centered on UPMC patient data, we help to guard against model instability issues on levels without observations early in the trial when fewer patients have been enrolled. The prior is parameterized to be weakly informative, such that as more patients are enrolled, the patient data quickly overwhelms the prior in the posterior estimation.

For each stratum-specific log odds ratio, we place a normal prior distribution with mean 0 and standard deviation of 1:

$$\beta_l \sim N(0, 1), l = 1, 2.$$

Additionally, for the covariates' log odds ratios,  $\kappa$ , we specify the same normal distributed prior with mean 0 and standard deviation 1:

$$\kappa_k \sim N(0, 1), k = 1, 2, \dots, p - 1.$$

This standard normal prior on the log odds ratio induces a relatively non-informative prior on the odds ratio that is lognormally distributed with a prior median of 1 (no effect). The prior assumes there is a 95% probability that the odds ratio effect is between 0.14 and 7.10.

We specify independent, normally distributed priors on the log-odds treatment effects:

$$\theta_t \sim N(0, 1), t = 1, 2, 3.$$

This prior on the log odds ratio induces a relatively non-informative prior on the odds ratio that is lognormally distributed with a prior median of 1 (no effect). The prior assumes there is a 95% probability that the odds ratio effect is between 0.14 and 7.10.

For the interaction term,  $\delta$ , we use the following prior:

$$\delta \sim N(0, \tau^2),$$

with the following prior on the variance term of the interaction:

$$\tau^2 \sim \text{IG}(0.8, 0.0525).$$

This inverse-gamma prior for  $\tau^2$  was chosen to encourage dynamic borrowing when learning the interaction term,  $\delta$ . This prior allows the data to determine the amount of information that is borrowed from the two individual interventions (RPM High and Enhanced team). If  $\tau^2$  is close to zero, then there is an additive effect for the combination arm with RPM high and Enhanced team; if  $\tau^2$  is positive, then we assume a synergistic effect between RPM high and the Enhanced team (effect of the combination is greater than the sum of the two interventions); if  $\tau^2$  is negative, this assumes an antagonistic interaction (effect of the combination is less than the sum of the two interventions). The prior shape 0.8 and prior scale 0.0525 were chosen such that the prior for  $\tau^2$  has a median of 0.1 with 90% probability of being less than 1.

#### 8.3.4. Model Stability

To assure model stability in the primary analysis model, the following modeling conventions may be taken at the statistical analysis committee's discretion.

- If there is an outcome in the ordinal scale that did not occur in the data, then that outcome will be combined with a neighboring outcome (the worse outcome). This is done for model stability. For example, if the outcome 11 never occurred, then a combined outcome of 10 & 11 will be modeled for the analysis.
- If a time bucket category has fewer than 5 patients observed in the category, it will be combined with the adjacent bucket (more recent bucket).

### 8.4. Posterior summaries

The following statistical quantities are used in the design of the trial. The posterior distribution of all model parameters is calculated using MCMC. The algorithm allows the generation of M (ex. 100,000) draws from the joint posterior distribution for all model parameters.

#### 8.4.1. Evaluation of posterior estimates

The Bayesian model of the primary endpoint described above is fitted to the data at each interim analysis. The posterior is calculated as:

$$p(\varphi|Y) \propto \prod_{i=1}^n p(Y_i|\varphi)p(\varphi),$$

where  $\varphi$  is the set of parameters for the primary endpoint model,  $p(\varphi)$  is the prior for those parameters,  $Y_i$  is the primary endpoint value for each patient, and  $n$  is the number of patients. The posterior is evaluated using MCMC using statistical software Stan.

#### 8.4.2. Probability of arm superiority over other intervention arms

For each of the four care model arms, we calculate the probability an arm is superior to other active arms using the posterior probability that each arm is optimal. This quantity is calculated from the M samples of the posterior distribution of the effect of each arm by reporting the proportion of posterior samples in which the odds ratio for arm  $t$  is the maximum observed effect across all non-STs treatment arms,  $t=1,...,4$ :

$$O(t) = \frac{1}{M} \sum_{m=1}^M I[OR_t < OR_j, \quad \text{for all } j \neq t], \quad t = 1, \dots, 4.$$

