**Aim 1b.** To determine the optimal care model (listed in Aim 1a) in terms of the number of days spent at home.

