## Randomization Procedure

The study will use web-based randomization to one of the five care models for those individuals who consent to participate in the study. Once a research coordinator determines eligibility, obtains informed consent, and the patient is discharged to home while maintaining eligibility, he or she will enter in key identification information, and the system will then generate a Study ID (numeric identification number) along with assignment to an intervention arm. Randomization will initially be fixed with 30% of patients randomized to STS and the remaining 70% of patients randomized 1:1:1:1 between the four RPM care models. After 250 patients have been randomized and followed for 90 days, the first interim analyses will be conducted and RAR will begin and continue to be updated every three months. During the RAR phase, the randomization to STS will remain fixed to be 30% of patients and the remaining 70% of patients will be randomized to one of the four RPM models preferentially based on the probability that each RPM care model is optimal.

While the research coordinators will see each assigned intervention arm per the randomization process, they will be blinded to overall changes in treatment allocation rates. Other study team members, including Principal Investigators, Co-Investigators, statistical analysts, and database administrators will also be blinded to treatment allocation rates during the course of data collection.

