#### Primary analyses

- For Aim #1, the primary analyses will be to compare PDHD between the 5 study arms (STS and the 4 experimental intervention arms):
  - **Aim 1a:** Efficacy will be evaluated by comparing PDHD between the STS arm and each of the 4 experimental arms, adjusting for illness severity (mechanical ventilation + vasopressors) and discharge location (whether patient went to SNF prior to home) and accounting for multiple comparisons
  - **Aim 1b:** Superiority of each experimental arm over the others will be evaluated by calculating the posterior probability that PDHD for each arm is greater than the others, adjusting for illness severity

(mechanical ventilation + vasopressors) and discharge location (whether patient went to SNF prior to home).

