The parameters  $\theta_1, \theta_2, \theta_3$  are log odds ratios for active interventions and the parameter,  $\delta$ , is an interaction effect between RPM high and enhanced team. We assume that the effects of each intervention are constant across strata and can be explained by a proportional log-odds ratio shift in the home days distribution. Each intervention's treatment effect is made up of components of the parameters, such that the treatment effect for RPM low/standard is equal to  $\theta_1$ , the effect for RPM high/standard is equal to  $\theta_1 + \theta_2$ , the effect for RPM low/enhanced is equal to  $\theta_1 + \theta_3$ , and the effect for RPM high/enhanced is equal to  $\theta_1 + \theta_2 + \theta_3 + \delta$ . We report these treatment effects as odds ratios, where  $OR_1 = \exp(\theta_1)$  is the odds ratio for RPM low/standard,  $OR_2 = \exp(\theta_1 + \theta_2)$  is the odds ratio for RPM high/standard,  $OR_3 = \exp(\theta_1 + \theta_3)$  is the odds ratio for RPM low/enhanced, and  $OR_4 = \exp(\theta_1 + \theta_2 + \theta_3 + \delta)$  is the odds ratio for RPM high/enhanced. The model is parameterized such that an odds ratio greater than 1 indicates that the care model is beneficial compared to STS.

The variables,  $Z_{i1}$  and  $Z_{i2}$ , are indicators of disease strata for patient  $i$ , where  $Z_{i1} = 1$  when a patient has severe illness (spent time on mechanical ventilation or vasopressors while hospitalized) and  $Z_{i1} = 0$  otherwise, and  $Z_{i2} = 1$  if patient  $i$  has been discharged to a SNF and  $Z_{i2} = 0$  if the patients is discharged immediately to home. With the above model, we assume that the underlying distribution of home days is different within each stratum, and that those differences can be explained by a proportional log-odds ratio shift in the home days distribution through the parameters,  $\beta_1$  and  $\beta_2$ .

Finally,  $p$  additional covariates,  $W_{iCOV}$ , are included in the model with parameters,  $\kappa$ .  $W_{COV}$  contain indicator variables for time at randomization, measured in buckets of 3-month intervals. The first time bucket (furthest in past) will be used as the referent in the model.

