## 8.7. Randomization

Initial randomization is set so that 30% of patients are randomized to STS and 70% of patients are randomized equally to the remaining 4 arms. After a burn-in of 250 patients, RAR will begin. The allocation to STS will be maintained at 30% throughout the course of the trial. The remaining 70% of patients will be allocated to the 4 active arms preferentially based on the probability that the intervention is superior to the other active arms as defined in Section 8.4.2.

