### 8.9.1. *Final analysis of primary endpoint*

The primary analysis of PDHD will consist of the posterior probability of superiority of each active arm over STS following posterior calculation from the model in Section 8.9.1. Success will be declared at the final analysis when all patients have observed their primary endpoint if the posterior probability of any care model relative to STS is greater than 0.991. This threshold was determined through simulation to assure the type I error is controlled at a 2.5% level. Specifically, we simulated 10,000 trials under the null scenario and find the threshold that controls overall 2.5% type I error (probability of declaring success under the null) across the simulated trial scenarios (Appendix Table 4).

We will also calculate the posterior probability that each active arm is superior to the other active arms (Section 8.4.2).

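### The Section 8.4.2 formula for the best care model has its inequality reversed: as printed, it gives the probability that an arm is the worst

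*Combined protocol and SAP*

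**What the plan says.** SAP Section 8.4.2 defines O(t), the quantity used to rank the four active arms. In words, it is the share of posterior draws in which the odds ratio of arm t "is the maximum observed effect across all non-STs treatment arms". The displayed formula averages a different indicator: "I[OR_t < OR_j, \quad \text{for all } j \neq t".

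The direction of benefit is fixed in Section 8.3.2: "an odds ratio greater than 1 indicates that the care model is beneficial compared to STS".

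Two later sections take the quantity from 8.4.2 by number:

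- Section 8.7 allocates the adaptive 70% of patients "preferentially based on the probability that the intervention is superior to the other active arms as defined in Section 8.4.2".
- Section 8.9.1, on the final analysis, says: "We will also calculate the posterior probability that each active arm is superior to the other active arms (Section 8.4.2").

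The second use answers Aim 1b, which the protocol states as "To determine the optimal care model (listed in Aim 1a) in terms of the number of days spent at home". The protocol's Randomization Procedure describes the adaptive allocation as made "preferentially based on the probability that each RPM care model is optimal".

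**The concern.** The sentence and the formula in 8.4.2 describe opposite events. The sentence picks out the arm with the largest odds ratio, and the formula picks out the arm with the smallest. On this trial's scale the smallest odds ratio belongs to the least effective care model.

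Section 8.4.2 is the only place where the between-arm probability is written as a formula. A programmer who codes the formula and not the sentence would steer the adaptive 70% of patients toward the worst active arm, and would report that arm as optimal under Aim 1b. Sections 8.9.3 to 8.9.6 ask for arm-versus-other-arms probabilities on secondary endpoints and give no formula of their own, so the slip could carry over to them.

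**Working it through.** **Direction of the sign**

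1. The model in 8.3.2 subtracts the treatment effect from the intercept for the log odds of having j or fewer home days. A larger log odds ratio therefore means more home days, as the text says.
2. Apply both versions to scenario 3 of Table 3, with true odds ratios 1.0, 1.0, 1.0 and 1.5 for arms 1 to 4. As data accumulate, the printed indicator for arm 4 asks whether 1.5 < 1.0, so O(4) tends to 0. The worded definition asks whether 1.5 is the largest, so O(4) tends to 1.
3. The neighbouring formulas agree with their own wording: 8.4.3 (superiority over STS) uses OR > 1 and 8.4.4 (harm) uses OR < 1. Only 8.4.2 is reversed. A fault in reading the PDF is therefore unlikely, and the published page will settle it.

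**Size if coded literally**

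Inputs from the SAP:

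- Table 2 outcome distribution; strata of 11% and 37% with odds ratios 0.75 and 0.35 (12.2)
- accrual of 70 patients per month to 1,500 (12.4)
- first look at 250 patients with 90 days of follow-up, then every 3 months (8.6)
- STS fixed at 30% (8.7)
- success threshold 0.991 (8.9.1)
- factorial model with N(0,1) priors on the main effects, and an interaction with variance prior IG(0.8, 0.0525) (8.3.3)

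Assumptions of the check: the 70% is split in proportion to O(t), because 8.7 does not state the mapping; log odds ratios are treated as normal; there are no time-bucket terms and no futility rule; 1,000 trials per scenario.

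The variance per patient on the log-odds scale is V = 3/(1 − Σp³). For the Table 2 baseline, Σp³ ≈ 0.454³ + 0.228³ + 0.133³ + smaller terms ≈ 0.108, so V ≈ 3.36. Averaging the information over the strata gives V ≈ 3.28. An arm of n patients contributes variance V/n.

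The plan's own figures come first, then the same simulation with each rule:

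| Scenario | Quantity | Table 5.1 | Maximum (wording) | Minimum (printed formula) |
|---|---|---|---|---|
| 2, One Weak | mean N, arm 4 | 458 | 457 | 150 |
| | overall power | 0.308 | 0.273 | 0.144 |
| | arm 4 named best | 0.854 | 0.840 | 0.008 |
| 3, One Expected | mean N, arm 4 | 607 | 603 | 109 |
| | overall power | 0.847 | 0.835 | 0.301 |
| | arm 4 named best | 0.991 | 0.986 | 0.000 |
| 4, One Strong | mean N, arm 4 | 694 | 696 | 93 |
| | overall power | 0.988 | 0.993 | 0.543 |
| | arm 4 named best | 0.999 | 0.999 | 0.000 |
| 6, Two Expected | mean N, arms 2 and 4 | 410, 420 | 411, 418 | 110, 109 |
| | overall power | 0.919 | 0.920 | 0.607 |
| | arm 2 or 4 named best | 0.998 | 1.000 | 0.001 |

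For scenario 3 the full mean sample sizes (STS, arms 1 to 4) are:

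- Table 5.1: 450, 130, 156, 158, 607
- maximum rule: 451, 131, 159, 156, 603
- printed rule: 450, 380, 287, 274, 109

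Two figures agree less closely. Scenario 2 power is 0.273 against the stated 0.308. The null success rate is 0.029 against 0.023, with a simulation standard error of about 0.005. Neither affects the direction, since the allocations match Table 5.1 under the maximum and are far from it under the minimum.

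**The case against.** The strongest reply is that this is one wrong symbol among consistent wording. The heading and sentence in 8.4.2, Sections 8.1 and 8.7, and the protocol's Randomization Procedure all give the right direction. Section 12.5 describes allocation moving toward the stronger arm, and the tables confirm it. At the final analysis each arm's odds ratio is reported too, so an inverted best arm would show the lowest odds ratio in the same results. All of this stands. It limits the point to the specification and makes the intended rule clear.

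It does not make the formula harmless. Sections 8.7 and 8.9.1 cite 8.4.2 by number, and the documents do not say that the simulation code is also the production code.

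A reader might infer three stronger things that the documents do not support:

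- **That patients were sent to the worst arm.** No allocation code or allocation data are shown, and the only visible evidence, the simulation tables, used the maximum.
- **That blinding would have hidden an inverted rule.** The protocol and SAP 7.2 blind study staff to allocation rates, but 7.2 restricts blinding to arm totals to employed, non-consultant statisticians. The DSMB receives interim reports (protocol, Study Oversight and the Payer paragraph under Measures) and primary-endpoint data by intervention (SAP 9.2). The documents do not show that an inversion would have gone unnoticed.
- **That reusing O(t) in 8.4.2 to 8.4.4 leaves the rule ambiguous.** Each use has its own titled subsection and is cited by number, so separate symbols are a preference.

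**Conclusion.** The inequality in 8.4.2 is reversed, and the formula as printed contradicts its own definition. That much follows from the text and rests on no assumption. Because the formula feeds the adaptive allocation and the Aim 1b comparison, it should be corrected.

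The size is conditional on literal coding. In scenario 3 the only effective arm would fall from about 603 to about 109 patients, overall power from 0.835 to 0.301, and the chance of naming that arm best from 98.6% to 0.0%. These figures rest on the normal approximation and on allocation proportional to O(t).

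The operating characteristics in Tables 5.1 and 5.2 need no change on this account. Success against STS is judged by the separate quantity in 8.4.3, and the published allocations reproduce only under the maximum. The finding is a specification error, and it is not evidence of misallocation.

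**What to change.** - In Section 8.4.2, change the indicator to I[OR_t > OR_j for all j ≠ t].
- Have the statistician with unblinded access confirm, and record in writing, that the production allocation code used the maximum at every update and that the final-analysis code does so for Aim 1b and the secondary between-arm probabilities.
- Optionally, give the three quantities in 8.4.2 to 8.4.4 different symbols and cite them by name in 8.7, 8.8 and 8.9.1.

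The cost is one character in the SAP and a short code check. No simulation needs to be rerun. The protocol timeline ends implementation on October 31, 2024. If that held, the allocation check is retrospective, and the correction matters mainly for the final analysis.

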#### 8.4.3. Probability of arm superiority over STS

To determine if the trial is successful at the final analysis, we summarize the posterior probability that each care model arm is superior to STS. The probability of superiority is calculated as the proportion of the M samples of an intervention's OR treatment effect that are greater than 1:

$$O(t) = \frac{1}{M} \sum_{m=1}^M I[OR_t > 1], \quad t = 1 \dots, 4.$$

#### 8.4.4. Probability of harm

To determine if an arm is futile at an interim analysis, we summarize the posterior probability that each care model arm is harmful compared to STS. The probability of harm is calculated as the proportion of the M samples of an intervention's OR treatment effect that are less than 1:

$$O(t) = \frac{1}{M} \sum_{m=1}^M I[OR_t < 1], \quad t = 1 \dots, 4.$$

### 8.5. Proportional odds assumption

The ordinal logistic regression model assumes that the effect of a treatment on the odds of higher PDHD is the same for all levels of the outcome. For example, this assumption entails that the effect of an intervention on the odds of surviving through the 90-day post discharge period increases by an amount proportional to the odds of having greater than 80 PDHD. In the event that the interventions have no effect on survival, but a beneficial effect on PDHD among survivors, the proportionality assumption will be violated.

#### 8.5.1. Assessing the proportional odds assumption

Assessment of the proportional odds assumption will occur once all patients are enrolled, or the study is ended for futility of one or more active arms over STS. We will dichotomize the endpoint at each level of the PDHD outcome, summarizing the odds ratio for each dichotomization and plotting for visual inspection of equality. Meaningful shifts in odds ratios across the ordinal scale will be interpreted as evidence of non-proportionality.

#### 8.5.2. Extending the proportional odds model

To assess the proportional odds assumption around the lower end of the distribution, we propose the following non-proportional model in Equation (2):

$$\text{logit}(\gamma_{i,j}) = \alpha_j - (X_{i1}(\theta_{1,k} + \theta_{2,k}X_{i2} + \theta_{3,k}X_{i3} + \delta_kX_{i2}X_{i3}) + \beta_1Z_{i1} + \beta_2Z_{i2} + W_{i,COV} \boldsymbol{\kappa}), \quad k = -1, \geq 0. \#(2)$$

where we allow the treatment effect to vary for death ( $k = -1$ ) and stay constant across the home-days distribution (0-90). The effects for strata are constant across the full scale, -1:90.

This proposed model results in the probability of death for patients on STS equal to:

$$\Pr(Y_i = -1) = \text{logit}^{-1}(\alpha_{-1} - (\beta_1Z_{i1} + \beta_2Z_{i2} + W_{i,COV} \boldsymbol{\kappa}))$$

And the probability of death for patients on a treated arm:

$$\Pr(Y_i = -1) = \text{logit}^{-1}(\alpha_{-1} - (X_{i1}(\theta_{1,-1} + \theta_{2,-1}X_{i2} + \theta_{3,-1}X_{i3} + \delta_{-1}X_{i2}X_{i3}) + \beta_1Z_{i1} + \beta_2Z_{i2} + W_{i,COV} \boldsymbol{\kappa})).$$

Then the remainder of the 90-day home days scale can be described using the usual proportional odds shift, for

$j = 1, \dots, 89$ :

$$\Pr(Y_i \leq j) = \text{logit}^{-1}(\alpha_j - (X_{i1}(\theta_{1,\geq 0} + \theta_{2,\geq 0}X_{i2} + \theta_{3,\geq 0}X_{i3} + \delta_{\geq 0}X_{i2}X_{i3}) + \beta_1Z_{i1} + \beta_2Z_{i2} + W_{i,COV} \boldsymbol{\kappa})).$$

The priors will be the same as specified in Section 8.3.3 for each level of the log-odds treatment effects,  $\theta_k$ .

The qualitative interpretation of this model will be similar to the primary analysis model above; however, this formulation will allow us to assess how these interventions impact mortality versus the time at home.

Analyses of mortality and PDHD among survivors from the model in equation (2) will be considered separate secondary analyses. See Section 8.9.3 below.

